### Ethical Considerations

This study has been approved by the Clinical Research and Ethics Committee of the Cork Teaching Hospitals (ECM 01/2023 PUB). The study poses a low risk to patients and does not interfere with any of the treatments that the patients will receive. Data will be stored in line with University College Cork standards and requirements.

A standardized consent form and patient information leaflet will be given to the patients, and they will be briefed on the project through information presented on the survey before they begin answering questions. Patients’ involvement will be fully voluntary and they will be given the option to withdraw from participation at any time. The researchers’ contact information will also be given to the patients so that they have any questions answered that might come up throughout the study. Only the email addresses of the patients will be collected, as patients’ identifiers so that the patients can be followed up with. The data will be pseudonymized as a result. Data will be kept on University College Cork servers for 10 years, excluding the email addresses, which will be used for following up with patients and will be immediately deleted after study completion. Patients will not be compensated for participating in this study.

### Outputs and Dissemination

The study results will be disseminated through international peer-reviewed research journals and local conference presentations.

## Results

Data collection began on February 14, 2023. As of February 12, 2024, 71 of 80 patients have been given the presurvey. The follow-up will begin once 80 patients have completed the presurvey. This is expected to be completed in March 2024 and the follow-up is expected to conclude in March 2025. General surgeons will then complete their surveys and interviews in March and April 2025. The overall expected completion date of the study is in April 2025.

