**Results:**

Data collection began on February 14, 2023. As of February 12, 2024, 71 of 80 recruited patients have been given the presurvey. The follow-up with the patients and the general surgeon components of the study have not begun. The expected completion date of this study is in April 2025.

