#### Recruitment of Patient Participants

Participants will be recruited using a nonprobability convenience sampling approach. The patients undergoing elective LCs will be viewed from the daily theater list and through communication with the operating surgical team*.* Participating patients will be identified as eligible by surgeons from Cork University Hospital who are collaborating in this study. The participant information sheet and consent form will be integrated into the beginning of the Qualtrics survey.

After completion of the presurvey, the participants will be sent a link for the postsurvey 12 months later through email. The recruitment and data collection flow for patients is presented in Multimedia Appendix 1.

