#### Patient Participant Survey

The survey will be based on the PROM questionnaire, which measures the effect of different factors on the PROs [10]. The following factors will be measured using the PROM survey: (1) age, sex, education level, marital status, employment status, ethnicity, smoking, and exercise frequency; (2) procedure perception; (3) hospital experience perception (PREMs); and (4) perception of longer-term consequences.

In addition, the acceptability and perceived value of the PROMs will be assessed with a survey from Stover et al [28].

The presurvey will be administered electronically by email using Qualtrics to patients who have completed an elective LC within the past 48 hours. These patients will then be followed up after 1 year and the survey will be administered again (Multimedia Appendix 2).

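### The Results section holds all follow-up until 80 presurveys are complete, which conflicts with the per-patient 12-month postsurvey in Methods and makes the earliest patients a few weeks late

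*Protocol article*

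**What the plan says.** Two sections of Methods set a clock for each patient. Recruitment of Patient Participants says: "After completion of the presurvey, the participants will be sent a link for the postsurvey 12 months later through email". Patient Participant Survey says the same in other words: "These patients will then be followed up after 1 year and the survey will be administered again".

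The Results section sets a condition on the whole cohort: "The follow-up will begin once 80 patients have completed the presurvey". It continues: "This is expected to be completed in March 2024 and the follow-up is expected to conclude in March 2025".

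On progress, Results says "Data collection began on February 14, 2023" and "As of February 12, 2024, 71 of 80 patients have been given the presurvey". The Abstract gives the same count ("71 of 80 recruited patients have been given the presurvey") and adds: "The follow-up with the patients and the general surgeon components of the study have not begun".

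The visible text gives no exception for patients who reach 12 months before the 80th presurvey is complete.

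**The concern.** A rule tied to each patient's own date and a rule tied to the 80th patient agree only if recruitment finishes within 12 months of the first presurvey. Recruitment has run longer than that, so for the earliest patients the two rules give different dates and only one can be followed.

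Two uses of the follow-up data are affected. The second study objective is whether patients can be followed up by email, so the 1-year response rate is a main result. If some links go out after 12 months, that rate mixes contact times. Data Analysis also compares each patient's first and second answers. With the trigger in place the interval between them is longer for the earliest patients and 12 months for the rest, so interval is tied to enrolment date.

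The wording adds a second difficulty. Progress is reported as presurveys given, while the trigger counts presurveys completed. The article does not say how many of the 71 were completed.

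**Working it through.** **Inputs, all from the Protocol article**
- Start of collection: February 14, 2023 (Results). Taken here as the date of the first presurvey, which is an assumption.
- 71 presurveys given by February 12, 2024; target 80 (Results).
- Trigger expected in March 2024; follow-up expected to end in March 2025 (Results).
- Postsurvey at 12 months from the patient's own presurvey (Recruitment of Patient Participants).
- Planned collection period: 10 months (Sample Size).

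Uniform accrual is assumed throughout, and a month is 30.4375 days.

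**1. Reproduce the stated March 2024 date**
- February 14, 2023 to February 12, 2024 = 363 days.
- Rate = 71 / 363 = 0.1956 per day, or 5.95 per month.
- Remaining 80 − 71 = 9 patients; 9 / 0.1956 = 46 days.
- February 12, 2024 + 46 days = March 29, 2024. This agrees with the article.

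**2. Delay for the first patient**
- Due date: February 14, 2024. Delay = trigger date − due date.
- Number late = rate × delay, that is, the patients enrolled in the first 16 to 46 days.

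| Trigger date | Delay, first patient | Interval, first patient | Patients late |
|---|---|---|---|
| March 1, 2024 | 16 days | 12.5 months | 0.1956 × 16 = 3.1 |
| March 29, 2024 (observed rate) | 44 days | 409 / 30.4375 = 13.4 months | 0.1956 × 44 = 8.6 |
| March 31, 2024 | 46 days | 13.5 months | 0.1956 × 46 = 9.0 |

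The conflict itself needs no accrual rate. The stated start date and any date in March 2024 are enough.

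**3. Given versus completed**

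At the observed rate, 0.1956 × 411 = 80.4 presurveys are given by March 31, 2024. Reaching 80 completed by then needs 80 / 80.4 = 99.5% completion. The article reports no completion rate, so the rates below are assumptions. Let c be the share completed, with recruitment going on at the same pace. Days from start to trigger = 80 / (0.1956 × c), and number late = 0.1956 × c × delay.

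| Assumed c | Trigger date | Delay, first patient | Interval, first patient | Patients late |
|---|---|---|---|---|
| 100% | March 29, 2024 | 44 days | 13.4 months | about 9 |
| 90% | May 13, 2024 | 89 days | 14.9 months | about 16 |
| 80% | July 9, 2024 | 146 days | 16.8 months | about 23 |
| 70% | September 20, 2024 | 219 days | 19.2 months | about 30 |

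**4. Had accrual gone to plan**

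Ten months from February 14, 2023 is December 14, 2023, which is 62 days before the first due date. Nobody would have been late. The trigger does harm only because accrual passed 12 months.

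**The case against.** The strongest reply is that the effect is small. On the stated dates about 71 or more of the 80 patients can still be surveyed at 12 months, and the rest are late by at most about six and a half weeks. The discussion of limitations cites 28% completion at 1 year in an earlier email study. Suppose (an assumption) that 9 late patients reply at half that rate. The overall rate is then (71 × 0.28 + 9 × 0.14) / 80 = 26.4%, a fall of 1.6 points. The sampling error of 28% in 80 patients is 1.96 × √(0.28 × 0.72 / 80) = 9.8 points either way. The comparison of first and second answers is within patient, so uneven intervals add some heterogeneity, and no bias has been shown. This stands, and it limits the severity.

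The Results paragraph can also be read as a loose account of study phases. The statement that follow-up had not begun by February 12, 2024 is correct under either rule, since nobody was yet due. The data collection flow in Multimedia Appendix 1 is not shown and may settle the timing. This softens the point, but the visible sentences still conflict.

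Two stronger inferences are tempting and are not supported:
- **That every patient waits until 12 months after the 80th presurvey.** The first patient would then be surveyed at about 24.5 to 25.5 months. The article does not say this. It has follow-up starting when the 80th presurvey is complete and ending in March 2025, which fits links sent on a rolling basis.
- **That the trigger pushes the study past April 2025.** If the 80th presurvey came in July 2024, that patient's own 12 months would end in July 2025 with or without the trigger. Such an overrun would come from slow accrual.

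**Conclusion.** The conflict is real on the article's own dates. Following the Results section as written surveys the earliest patients late and departs from the 12-month rule in Methods. With a March 2024 trigger the first patient is 16 to 46 days late, and roughly 3 to 9 of 80 patients are affected (about 9 at the observed rate), with the delay shrinking to zero. This rests on a first presurvey on February 14, 2023 and uniform accrual.

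The longer delays in the working depend on completion rates that the article does not give. They show what the loose use of given and completed could cost, not what is expected. That late contact lowers response is plausible but not shown.

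Severity is moderate to minor. The point deserves correction because a 12-month contact that has been missed cannot be recovered, and because it touches the timing of a stated objective.

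**What to change.** - Remove the 80-completed trigger from the Results section, so that it agrees with the two Methods sections. Send each postsurvey link at 12 months from that patient's own presurvey, whatever the state of accrual.
- State whether the target of 80 means presurveys given or completed, and report progress in the same unit.
- For any link already sent late, report the actual interval between the two surveys.

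The cost is one corrected sentence, one definition and an email schedule run by patient date. No patients are added. On the assumptions above, the first link is due on February 14, 2024. If the 80th presurvey is completed in March 2024, the last is due in March 2025, so the stated end of follow-up does not move.

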## Discussion

### Study Significance and Strengths

This study will convey the perspective of participants regarding which PROs are most important for them after LCs. Based on prior research, we expect the technical skill and experience level of the surgeon, long-term quality of life, patient involvement in decision-making, communication skills of the surgeon, cleanliness of the ward environment, and standards of nursing care to be the most important factors for the patients [10]. Furthermore, this study will indicate the acceptability and perceived value of participants regarding electronic PRO surveys, which is a topic that is relatively more limited in the literature in the context of LCs. The study has well-defined inclusion and exclusion criteria, with all patients being given the survey less than 48 hours after their surgery and only elective cases being included. This will help make the sample more homogenous, as patients undergoing emergency surgery might have different perspectives on what is important for them in comparison to those having elective surgery [11].

Furthermore, the long-term follow-up of 1 year will assist in better understanding the views of patients undergoing LC. The distribution of the survey to postoperative patients will ensure that the patients already had the experience of having an LC and can reflect upon it when answering the survey. This perspective would not be achievable with patients in a preoperative setting. The use of a 50-item survey also ensures that several PROs and factors will be analyzed, thereby offering a broad view of patients’ perspectives on PROs. Moreover, the integration of the perspectives of surgeons regarding the study may help elucidate improved procedures when following up with patients.

### Limitations

As a result of this being a feasibility study, there are several associated limitations. Primarily, the small sample size of 80 participants will limit the generalizability of the study. Moreover, the use of convenience sampling also limits the external validity and generalizability of the results. It has been shown that convenience sampling has greater validity when the sample is more homogenous with respect to the participants’ sociodemographic characteristics [31]. However, making the sample completely homogenous in this study would result in an inadequate sample size. Thus, this bias will be mitigated through statistical analyses exploring differences in the factors that are deemed important according to the participants’ demographic characteristics. Another significant bias associated with using convenience sampling is that the participants accepting to partake in the study could be more likely to find perceived value in completing the electronic survey in comparison to those who declined to participate. These biases will be mitigated through the use of rigid inclusion and exclusion criteria, ensuring that the sample is as homogenous as possible.

Another limitation is the use of a 4-point Likert scale. Likert scales ideally have between 4 and 7 options, although 4-point scales might commit participants to give answers they may not wish to give [32].

Although only including patients undergoing elective surgery will aid in further defining the inclusion and exclusion criteria, this restriction will also limit the generalizability of this study, as patients undergoing emergency LC will not be represented.

In addition, recruiting patients within 48 hours of their LC means that their postoperative condition could influence their answers. The survey also contains mild medical jargon (eg, “bile leak”) that might be confusing for participants.

There is no electronic literacy scale for the participants involved. Incorporation of such a scale would have improved the interpretation of the results by demonstrating whether the ability to use technology impacts the participants’ views on electronic surveys.

The lack of direct comparison with paper surveys is another potential limitation, as this prevents a comprehensive interpretation of the benefits of electronic surveys over paper surveys. Although this study addresses the difficulty that patients might have in using electronic devices, it does not address other major barriers to electronic PROs, such as inadequate information technology infrastructure and the time needed to complete the survey [17].

The survey from Stover et al [28] may also be biased toward favorable responses. The reason for this is that the study aimed to maintain a neutral response option, while also having only 4 options to be consistent with the other survey questions. For this reason, there is only one “negative” option.

Finally, the follow-up will also be very challenging due to the small sample size. A prior study exploring email-based PRO systems following hand surgery indicated that this approach may be effective [33], although only 28% of participants completed the follow-up PRO survey 1 year after their enrollment in the study. Despite the lack of valid generalizability of the email follow-up data in this study, the results will convey the feasibility of using email to distribute PRO surveys and help guide future studies with more robust samples.

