### Component 1: Patient Survey

#### Patient Participants

The subjects will include all patients who completed elective LCs from Cork University Hospital and Mercy University Hospital, both in Cork, Ireland. Patients undergoing LC were chosen for this study owing to the high number of LCs completed in these hospitals. This makes the study more feasible and realistic to complete.

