#### Inclusion Criteria

Patients must be >18 years old and have completed an elective LC. Patients must have the capacity to access the Qualtrics survey through their smartphone and have completed the LC within 48 hours of distribution of the first survey. For the sake of feasibility, any indication for the elective LC will be eligible for recruitment in this study to ensure an adequate sample size.

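### Eligibility criteria cannot mitigate self-selection on the perceived value of the electronic survey, although the Limitations section says they will

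*Protocol article*

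**What the plan says.** Objective 1 (Study Objectives) includes how acceptable and valuable patients find electronic patient-reported outcomes. The Limitations section recognises that, under convenience sampling, people who take part "could be more likely to find perceived value in completing the electronic survey in comparison to those who declined to participate". Its remedy follows at once: "These biases will be mitigated through the use of rigid inclusion and exclusion criteria, ensuring that the sample is as homogenous as possible".

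Four other statements bear on this:

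- Patient Participants defines the population broadly: "The subjects will include all patients who completed elective LCs from Cork University Hospital and Mercy University Hospital".
- Inclusion Criteria for patients narrows it: "Patients must have the capacity to access the Qualtrics survey through their smartphone". Recruitment of Patient Participants adds that the information sheet and consent form open the Qualtrics survey.
- On homogeneity, Inclusion Criteria says that "any indication for the elective LC will be eligible for recruitment in this study to ensure an adequate sample size", and the Limitations paragraph itself concedes that "making the sample completely homogenous in this study would result in an inadequate sample size".
- Limitations later says: "Although this study addresses the difficulty that patients might have in using electronic devices". The same section states that no electronic literacy scale is used.

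**The concern.** The bias named is a difference between accepters and decliners in the outcome being measured. The remedy offered controls who may be invited. It does not affect which of the invited patients respond. Two patients who meet every criterion can still differ in how much they value an electronic survey, and the one who values it less is the one more likely to decline.

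A second issue is distinct and should be kept apart. The smartphone criterion and consent inside the electronic instrument restrict the target population. That is a limit on generalisability, not volunteer bias among eligible patients. It matters here because this criterion belongs to the set offered as the remedy, and it removes the patients with least electronic access.

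At stake is how objective 1 is read. A reader told that the bias has been mitigated may take the acceptability figure as an estimate for elective LC patients in general.

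**Working it through.** **No plan figure to reproduce.** The target of 80 was set by feasibility (Sample Size). The article states no participation rate, expected acceptability or precision. All rates below are assumptions.

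**Step 1. Order of events.** A patient is identified as eligible, is emailed the link, meets the information and consent pages in Qualtrics, and completes or does not. The criteria act at the first step; the bias arises at the last two.

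**Step 2. Self-selection among eligible patients.** Let p be true acceptability among eligible patients, and a and b the participation probabilities of those who do and do not value the survey. Then

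p_obs = p·a / (p·a + (1 − p)·b).

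The bias vanishes for intermediate p only if a = b. Criteria may change p, but nothing in them makes a equal b. With p = 0.70 and a = 0.80:

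| b | p_obs | bias (points) |
|---|---|---|
| 0.80 | 70.0% | 0 |
| 0.60 | 75.7% | +5.7 |
| 0.40 | 0.56/0.68 = 82.4% | +12.4 |
| 0.20 | 90.3% | +20.3 |

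For comparison, the 95% sampling half-width at n = 80 and 80% acceptability is 1.96·√(0.8·0.2/80) = 8.8 points. Moderate self-selection could therefore exceed sampling error.

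**Step 3. Restriction to smartphone users.** Suppose 10% of elective LC patients lack access. If they would accept at the same 70%, the third row is unchanged at +12.4: the restriction removes none of the bias. If only 30% of them would accept, the all-patient figure is 0.9·0.70 + 0.1·0.30 = 66%, and the observed 82.4% is 16.4 points above it. Of this, 12.4 is self-selection and 4.0 (70 − 66) is the narrower population.

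**Step 4. What a participation count would allow.** With x favourable among n completers and N eligible, acceptability among the eligible lies between x/N (every non-completer unfavourable) and (x + N − n)/N (every non-completer favourable). Assume x = 72 and n = 80, so 90% of completers:

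- N = 100: 72/100 = 72% to (72 + 20)/100 = 92%.
- N = 130: 72/130 = 55.4% to (72 + 50)/130 = 93.8%.

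These bounds contain 90% and extend above it. They show how uncertain the figure is, not that it is biased upward.

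**The case against.** The authors disclose convenience sampling, limited external validity and the volunteer bias itself, so nothing is hidden. The mitigation sentence refers to biases in the plural. For sociodemographic heterogeneity, homogeneity is a rationale that the section supports with a citation. That stands: the sentence is wrong only as applied to self-selection on perceived value, which is the bias named immediately before it.

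Access to Qualtrics does not mean ease in using it, and the survey items are in Multimedia Appendix 2, which is not shown. Items on difficulty may exist, so the statement on device difficulty should be qualified and need not be withdrawn.

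A reader might infer more than the documents support:

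- **That surgeons select on acceptability.** The text says only: "Participating patients will be identified as eligible by surgeons from Cork University Hospital who are collaborating in this study". It gives them no discretion based on attitude to electronic surveys, and the direction of any effect is unknown.
- **That the plan lacks a denominator.** The recruitment flow is in Multimedia Appendix 1, which is not shown, and a screening log may sit in a full protocol. Its absence from an article is not an error.
- **That uptake is a main feasibility figure.** Objective 2 concerns follow-up by email; enrolment uptake is not a stated objective.
- **That invitations should now be consecutive.** By February 12, 2024, 71 of 80 patients had been given the presurvey, leaving 80 − 71 = 9.
- **That the result is biased upward.** The article says only that this could be so, and the data to show it are not given.

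**Conclusion.** The mitigation claim is wrong as written for the bias to which it is applied. This conclusion rests on the order of events alone and needs no assumed figure. The article also undercuts the claim by accepting any elective indication and by conceding that full homogeneity is out of reach.

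Separately, acceptability will be known only for patients who could reach the survey by smartphone and completed it. It cannot be carried over to all elective LC patients at the two hospitals.

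The size is unknown. Under the assumed rates with true acceptability of 70%, self-selection adds about 6 to 20 points. Bounds of 72% to 92%, or 55% to 94%, follow from an assumed 72 of 80 favourable with 100 or 130 eligible. The error affects the interpretation of objective 1. It does not invalidate the study, and it can still be corrected.

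**What to change.** 1. Delete the mitigation sentence, or reword it so that it does not claim to address volunteer bias.
2. State acceptability and perceived value as applying to smartphone-capable patients who completed the survey.
3. Qualify the Limitations statement on device difficulty as limited to patients able to access the survey.
4. From the theater lists already viewed and the Qualtrics distribution records, report the numbers listed, eligible, emailed and completed, as far as these can be recovered.
5. Give best- and worst-case bounds on acceptability among eligible patients, as in Step 4. Count patients without smartphone access separately and do not fold them into the bounds.

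The cost is a small tally from records already in use, with no new patient contact. The acceptability figure will be wider or less favourable, and counts for patients already enrolled may be incomplete.

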### Study Objectives

This study aims to explore the perspectives of patients and surgeons on the use of electronic PROMs. These perspectives will be investigated through the distribution of surveys to both groups and via the completion of interviews with the general surgeons.

The specific objectives of the study include (1) understanding the acceptability and perceived value of electronic PROs from the perspective of both patients undergoing LC and general surgeons and (2) determining the feasibility of following up with patients regarding their PROs using email correspondence.

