#### Data Analysis

SPSS v28.0.1.1 (IBM Corp) will be used to complete the data analysis for the patient surveys. The 4-point Likert-scale questions will be tallied into two categories of either “more important” or “less important.” Mean scores will be used to determine the most important and least important factors. Univariate analysis with χ^2^ tests will then be used to determine if any demographic relations exist between what PROs participants find to be more or less important. Additionally, the Wilcoxon ranked sign test and 2-tailed ANOVA will be used to compare the differences between the patients’ answers in their first and second survey responses.

Data from the survey for the surgeons will also be analyzed with SPSS. Mean scores will be tabulated for the general surgeons’ responses to the survey. For the general surgeons’ interviews, the results will be transcribed verbatim and analyzed with thematic synthesis [24]. The qualitative data will explain the overall view that surgeons have regarding PRO collection and the quantitative data will be analyzed in conjunction to illustrate the specific PROs that the surgeons view as important. The patient and surgeon data will also be integrated by comparing the views that both stakeholders have as indicated in the PROM surveys.

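### The one patient measure named for objective 1 has four options with only one negative, and the stated tally and mean for 4-point questions do not suit it

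*Protocol article*

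**What the plan says.** All references are to the protocol article.

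- **Study Objectives.** The first objective is "understanding the acceptability and perceived value of electronic PROs from the perspective of both patients undergoing LC and general surgeons".
- **Patient Participant Survey.** For patients, "the acceptability and perceived value of the PROMs will be assessed with a survey" adapted from a published source. The other blocks cover demographics, the procedure, the hospital stay and longer-term consequences. No second patient instrument for acceptability is named.
- **Limitations.** This survey "may also be biased toward favorable responses". The reason given is that "the study aimed to maintain a neutral response option, while also having only 4 options to be consistent with the other survey questions", so that "there is only one “negative” option". The same section notes separately that people who agree to take part may value the electronic survey more than those who decline. It claims mitigation for the sampling biases but states none for the response scale.
- **Data Analysis.** "The 4-point Likert-scale questions will be tallied into two categories", labelled by greater or lesser importance, and mean scores identify the most and least important factors. First and second responses are then compared. The acceptability items are neither named nor exempted.
- **Results.** By 12 February 2024 the presurvey had been given to 71 of 80 patients. According to the Abstract, follow-up had not begun.

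**The concern.** The patient half of objective 1 will be reported as how many patients view electronic outcome collection favourably. If two options are positive and one is negative, that figure may partly reflect the form. Volunteer selection, which the authors also acknowledge, would push the same way.

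The analysis rule adds a second problem. A two-category importance tally has to put neutral on one side or the other, and neither importance label describes a neutral view of acceptability. A mean on such a scale invites comparison with the scale midpoint, which is not the neutral point. Both choices could make an indifferent sample look supportive.

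**Working it through.** The article gives no figure for this point, so there is none to reproduce. The structure comes from the document. The response distributions below are assumptions that show a range.

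**1. Count the options.** Limitations gives 4 options, 1 neutral and 1 negative. Positive options = 4 − 1 − 1 = 2.

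**2. Locate neutral.** Assume equally spaced codes in order, expressed relative to neutral: −1, 0, +1, +2. The midpoint is (−1 + 2)/2 = +0.5. With 1-to-4 coding (also assumed, since no coding is stated), neutral is 2 and the midpoint is (1 + 4)/2 = 2.5. A mean at the midpoint therefore lies half a point on the favourable side.

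**3. Respondents with no net opinion, three ways of answering.**

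- *Even choice* across the options.
- *By label*: opinion is standard normal, with cut-points −0.5, 0.5 and 1.5. Shares are 0.309, 0.383, 0.242 and 0.067.
- *By position on the scale*: standard normal, with cut-points −1, 0 and 1. Shares are 0.159, 0.341, 0.341 and 0.159.

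| Answering | Favourable | Neutral | Unfavourable | Mean minus neutral |
|---|---|---|---|---|
| Even choice | 2/4 = 50% | 25% | 25% | (−1 + 0 + 1 + 2)/4 = 0.50 |
| By label | 24.2 + 6.7 = 30.9% | 38.3% | 30.9% | −0.309 + 0.242 + 2 × 0.067 = 0.067 |
| By position | 34.1 + 15.9 = 50.0% | 34.1% | 15.9% | −0.159 + 0.341 + 2 × 0.159 = 0.50 |

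On a balanced five-option scale, even choice gives 2/5 = 40% on each side and label-based answering gives 30.9% on each side. Both means are exactly at neutral.

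**4. Effect of where the tally puts neutral.** If neutral is grouped with the positives, the favourable share becomes 100% minus the unfavourable share:

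- even choice: 100 − 25 = 75%, instead of 50%;
- by label: 100 − 30.9 = 69.1%, instead of 30.9%;
- by position: 100 − 15.9 = 84.1%, instead of 50%.

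The grouping alone moves the headline by 25 to 38 percentage points in these illustrations. If the tally instead split the upper two options from the lower two, and the options run in order, neutral would fall with the negative. The article does not say which applies.

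**5. Effect of switching to five options at follow-up.** With even choice and unchanged opinion, the favourable share would go from 50% to 40%, a fall of 10 points produced by the form. With label-based answering it would stay at 30.9%.

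**The case against.** The strongest reply is that the authors disclose the asymmetry, its cause and its likely direction themselves, and say only that bias is possible. That stands. A reader might infer that the results are tilted, or tilted two to one, but the document does not support either. Even choice is a weak model of indifference when a neutral option is offered, and label-based answering produces no gap in proportions.

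A second reply is that the tally and mean were written for the importance items. Their labels fit those items, and Data Analysis never mentions acceptability. This is fair as to intent, so one cannot say that the authors chose the rule for these items. But the wording covers 4-point questions without exception, Limitations says these items have four options, and no other handling is stated. The same clarification is needed on either reading.

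Third, the survey itself (Multimedia Appendix 2) is not shown. The two positive options are a subtraction, the coding is assumed, and the claim to a single instrument means only that no other is named.

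Two further extensions fail. A reader might want a balanced five-option scale in the postsurvey. With most presurveys already given, this could create a spurious change in the planned first-versus-second comparison. A reader might also extend the point to surgeons, because Study Design and Overview speaks of the same survey. The more specific Surgeon Survey section limits their version to three blocks without acceptability items, and their attitudes come from interviews.

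Finally, this is a feasibility study, and no decision threshold stated in the article rests on these items. That limits the consequence but does not remove it, because acceptability is a stated objective.

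**Conclusion.** The point holds in a limited form. The one patient measure named for objective 1 uses an unbalanced scale that may lean toward favourable answers. No mitigation is stated, and the only rule given for 4-point questions does not suit it.

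Only the direction is supported. The size depends wholly on assumed answering behaviour: from no gap in proportions and a mean 0.07 above neutral, to 50% against 25% under even choice (50% against 15.9% if people answer by position). None of the three illustrations leans unfavourably. How neutral is grouped matters at least as much as the scale itself, and unlike the scale it can still be settled at almost no cost. The conclusion assumes that the options are ordered and, for the mean, equally spaced.

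**What to change.** Keep the same four options in both surveys, so that the within-patient comparison uses one form throughout. In Data Analysis:

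1. Exempt the acceptability and perceived-value items from the two-category importance tally and from mean scores.
2. Report the full four-category distribution at each survey, with neutral shown separately and never counted as favourable.
3. Compare first and second surveys on favourable versus neutral plus unfavourable, using a method for paired proportions.
4. State with the result that favourable proportions on this scale, in a self-selected sample, are likely to lean upward, and limit the objective 1 conclusion accordingly.

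The cost is a few lines of text, slightly more reporting and a less favourable headline. No new data are needed. Any lean in the scale itself remains, so it has to be carried in the interpretation.
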